## Abstract

**Background:**

Preoperative chemoradiotherapy (pre-CRT) followed by total mesorectal excision (TME) is currently a standard therapy for locally advanced mid-to-low rectal cancer. Less aggressive, organ-preserving option such as local excision (LE) or watchful wait can alternatively be used for patients who respond well to pre-CRT. High-resolution rectal magnetic resonance imaging (MRI) is one of the most useful methods to assess pre-CRT response, and the MERCURY group has shown that the MR tumor regression grade (mrTRG) correlated with the pathologic TRG. The aim of this study is to compare postoperative complication and oncologic outcomes between LE and TME in mid-to-low rectal cancer patients whose tumors are mrTRG grade 1 (radiological complete remission) or 2 (predominant fibrosis; near-complete remission) after pre-CRT.

**Methods:**

A prospective, double-arm, randomized, open-labeled, single center, clinical trial will be conducted in patients with mid-to-low rectal cancer whose tumors are mrTRG 1/2 after pre-CRT at the Asan Medical Center, Seoul, Korea, after approval from the Institution Review Board. Patient medical records will be de-identified using a serial number to protect personal information. Inclusion criteria will include rectal adenocarcinoma with an inferior border < 8 cm from the anal verge, mrTRG 1/2, age > 20, and provision of informed consent. Postoperative complications will be assessed by Clavien-Dindo Classification Grade. Oncologic and functional outcomes will be collected and risk factors related to these outcomes will be investigated.

**Discussion:**

We believed that the rate of postoperative complication of LE will be comparable to that of TME in mid-to-low advanced rectal cancer patients with a favorable response after pre-CRT.

**Trial registration:**

KCT0002579 (https://cris.nih.go.kr) Dec-2017.

## Background

In the treatment of rectal cancer, total mesorectal excision (TME) improves oncologic outcomes and adding preoperative chemo-radiotherapy (pre-CRT) to TME has been shown to effectively improve local control [1–4]. For this reason, pre-CRT followed by TME is recommended for patients with locally advanced mid-to-low rectal cancer [5–9]. However, significant complications are associated with TME, including anastomotic leak, sexual and urinary dysfunction, and frequent stool passage, on top of the peri-operative morbidity associated with all major surgery [10–12]. In addition, abdominoperineal resection (APR) involves a permanent stoma and low anterior resection (LAR) often involves at least a temporary stoma [8, 12, 13]. The decision of a surgical strategy must take oncologic outcomes, postoperative complications, and quality of life into account.

For patients with favorable responses to pre-CRT, organ-preserving strategies such as local excision (LE) and watchful waiting are becoming more accepted [14–19]. There has been some debate regarding the oncologic safety of LE following pre-CRT in advanced mid-to-low rectal cancer [14–18]. LE following pre-CRT for advanced rectal cancer could be a particularly good option for patients showing a complete pathologic response and achieving tumor regression not only in the primary tumor but also in the mesorectal metastatic lymph nodes [20–24]. Although the tumor regression grade (TRG) obtained using high-resolution rectal magnetic resonance imaging (mrTRG), as proposed by the MERCURY study group, correlated with the pathologic TRG [20, 21, 23, 24], mrTRG did not reflect the pathologic T status. A recent study from our institution showed that a status of mrTRG1 predicted a pathologic complete remission (pCR) with 60.6% accuracy and the projected completion TME rate of mrTRG1 was 25.6%. This results suggests that LE, compared with watchful wait, is more likely to result in pCR [25].

There have been several reports on the feasibility of performing LE following pre-CRT, most of which are focused on either clinical T2–3 rectal cancer or on cases of pCR [26–28]. However, the oncologic safety of LE in patients with a pathologic early T status after pre-CRT has not been established [29]. Therefore, data on long term outcomes with respect to the pathologic status and the type of surgery in patients with locally advanced rectal cancer is needed.

## Methods

### Objective

The purpose of the current study is to determine whether LE in mid-to-low rectal cancer patients with mrTRG 1 or 2 tumors after pre-CRT is safe and effective in terms of surgical and oncologic outcomes.

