#### Secondary study endpoints

1. Disease-free survival rate (%), overall survival rate (%) and recurrence rate (%) at 3 years.

2. Functional outcomes, including quality of life (EORTC-E030) and score of fecal incontinence (Wexner’s score) at 6, 12 and 24 months after surgery.

3. Rate of permanent stoma formation (%) at 3 years.

4. Accuracy of mrTRG (positive predictive value and negative predictive value).

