#### Sample size calculation

The sample size was calculated based on two-sided non-inferiority test with for 80% power and a significant level of 0.05, one-sided. We assume that the rate of postoperative complications on day 30 will be 15% in the TME group and 15% in the LE group, with a non-inferiority margin of 15%. Based on these calculations, a total of 67 patients should be allocated to each group; assuming a 5% dropout rate, we plan to enroll 140 patients. The 15% rate of postoperative complications cited above is based on published findings [26–28, 30].

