### Data analysis

The intent-to-treat (ITT) analysis set will include all subjects who are randomized into a surgery group. The modified ITT analysis set will include all subjects who undergo pre-CRT. The per protocol (PP) analysis set will include only the subjects in the ITT group who complete the study protocol. Patients who withdraw informed consent or who develop serious adverse events will be excluded from the PP analysis set. The modified ITT set will be used for analysis of primary and secondary study endpoints. The PP analysis set will be used for subgroup analysis. Baseline characteristics will also be analyzed in the ITT group.

Variables and outcomes will be analyzed using chi-square tests (for proportions) or Fischer’s exact test, as appropriate. Continuous data will be analyzed using Student’s t-test or Mann-Whitney U tests, as appropriate. Cumulative risk rates will be calculated using the Kaplan-Meier method and compared using log-rank tests. Multivariate analyses using binary logistic regression will be used to assess the risk of postoperative complications. Statistical significance will be defined as *p* < 0.05, and all analyses will be performed using SPSS software, version 22 (IBM Corporation, Armonk, NY, USA).

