Previous studies, even prospective studies for LE or watchful waiting, suffer from the lack of standardized selection criteria. Recently, the MECURY group convened multidisciplinary teams (MDT) to decide which patients should defer surgery and which patients should receive standard treatemtn after pre-CRT [22]. Our institution also reported that case discussions in MDT meetings resulted in altered clinical decisions in > 10% cases for advanced and recurrent colorectal cancer [32]. Based on this experience, in the current study, specialized faculty, including a colorectal surgeon, radiologist, medical oncologist, radiation oncologist, gastroenterologist, and pathologist, will select the study patients that show a favorable response after pre-CRT. The data on postoperative complications in LE and TME after pre-CRT collected through the current study will provide valuable information about the risk factors of LE after pre-CRT.

This prospective study has some weaknesses because this study will be performed based on the real practice in our institution. Recent studies insists that the interval between completion of pre-CRT and the assessment of tumor response is increased up to 12 weeks and this longer interval might increase the rate of pathologic CR [33, 34]. On the other hand, in this prospective study, TME is undertaken 6–8 weeks after the completion of pre-CRT according to the real practice in our institution. The schedule of restaging is designed within 2 weeks before surgery considering waiting time of MRI in our institution and minimizing dropouts, however, almost patients have restaged at 2 or 3 days before surgery on the real practice. About 10% of lymph node infiltration and the 15% of local recurrence in the ypT2 were worrisome for this study [27, 29, 35]. Nevertheless, recent reports showed the overall survival was not significantly different between the LE and TME groups [27, 36, 37]. The evidences of LE for ypT2 tumors are still lack, therefore, our study determines the effect of LE in ypT2 tumors on oncologic outcomes.

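### The objective and the Discussion promise a determination of oncologic safety, but the trial is sized for 30-day complications and the stated survival comparison is a log-rank test with no margin, which cannot show that LE is not worse

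*Protocol article*

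**What the plan says.** All references are to the protocol article.

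- **Objective (Methods):** the trial is to determine whether LE in patients with mrTRG 1 or 2 is "safe and effective in terms of surgical and oncologic outcomes".
- **Background:** the gap to be filled is that "the oncologic safety of LE in patients with a pathologic early T status after pre-CRT has not been established".
- **Discussion, last paragraph:** "our study determines the effect of LE in ypT2 tumors on oncologic outcomes".
- **Sample size calculation:** the only hypothesis with a margin concerns complications at day 30, with 15% assumed in each arm and a 15-point margin. It is described as a "two-sided non-inferiority test with for 80% power and a significant level of 0.05, one-sided", and "a total of 67 patients should be allocated to each group; assuming a 5% dropout rate, we plan to enroll 140 patients".
- **Secondary study endpoints:** the oncologic outcomes are "Disease-free survival rate (%), overall survival rate (%) and recurrence rate (%) at 3 years".
- **Data analysis:** "Cumulative risk rates will be calculated using the Kaplan-Meier method and compared using log-rank tests", with significance at p < 0.05 and the sidedness not stated. There is no oncologic margin, event target or assumed DFS.
- **Investigational treatment of the experimental arm:** LE patients who go on to completion TME are evaluated with the TME group. Those who decline it are excluded and followed for a subgroup analysis.

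**The concern.** Whether LE is oncologically safe is a question of being not worse than TME. The protocol frames the complication question that way, with a margin. For survival it names only a test of difference. Such a test can reveal harm if there are enough events, but failing to reject does not show that harm is absent.

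With few events, a non-significant result would be compatible with a clinically important loss of DFS. The misreading is foreseeable. The Discussion meets its own worry about recurrence in ypT2 tumours by citing reports in which overall survival did not differ significantly, and the Safety section describes oncologic outcomes as regarded as equivalent. At stake is what may be concluded about replacing radical cancer surgery with a lesser operation.

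**Working it through.** **1. The plan's own figure.** For 15% versus 15%, margin 15 points, one-sided 0.05 and 80% power (unpooled variance):

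n per arm = 2 × 0.15 × 0.85 × (1.645 + 0.842)² / 0.15² = 70.07, rounded up to 71.

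The plan states 67, at which power is 78.4%. This small gap is a separate matter and does not affect what follows. No oncologic quantity enters the calculation.

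**2. Inputs for the oncologic check.**
- 67 per arm (Sample size calculation).
- 3 years of follow-up (Postoperative follow-up schedule).
- Log-rank test at 0.05 (Data analysis), taken as two-sided. One-sided values are also shown.
- TME 3-year DFS, S: **assumed**, 90% to 60%, because the document gives none.
- Hazard ratios 1.5 and 2: **assumed**, as illustrations of harm.

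**3. Events and power.** Under proportional hazards, LE 3-year DFS = S^HR.

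Events d = 67(1 − S) + 67(1 − S^HR). Two-sided power = Φ(√d/2 × ln HR − 1.96) (Schoenfeld).

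Worked case, S = 0.80, HR 1.5:
- LE DFS = 0.80^1.5 = 0.716.
- d = 13.4 + 19.1 = 32.5.
- Power = Φ(1.155 − 1.96) = 21%.

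| TME 3-year DFS (assumed) | LE DFS at HR 1.5 | Events | Power, two-sided 0.05 | Power, one-sided 0.05 | Simulated log-rank, two-sided |
|---|---|---|---|---|---|
| 90% | 85.4% | 16.5 | 13% | 21% | 12% |
| 80% | 71.6% | 32.5 | 21% | 31% | 20% |
| 70% | 58.6% | 47.9 | 29% | 40% | 27% |
| 60% | 46.5% | 62.7 | 36% | 48% | 35% |

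The simulation used 4,000 trials per row, with exponential times censored at 3 years. Across these rows, 64% to 87% of trials would show no significant difference on the two-sided test.

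**4. How far the result depends on the assumed DFS.** Power of 50% at HR 1.5 needs 4 × 1.96² / (ln 1.5)² = 93.5, so 94 events among 134 patients. That requires a TME 3-year DFS below about 38%. Power of 80% needs 4 × (1.96 + 0.842)² / (ln 1.5)² = 191 events, more than the 140 patients to be enrolled.

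**5. Larger harm, HR 2.**
- S = 0.80: LE DFS 64%, d = 13.4 + 24.1 = 37.5, power = Φ(2.123 − 1.96) = 56%.
- S = 0.90: d = 6.7 + 12.7 = 19.4, power = Φ(1.528 − 1.96) = 33%.
- S = 0.60: d = 26.8 + 42.9 = 69.7, power = Φ(2.893 − 1.96) = 82%.

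**6. Precision of the 3-year difference.** With equal true DFS and no censoring before 3 years, the half-width is 1.96 × √(2S(1 − S)/67):
- S = 0.90: 10 points.
- S = 0.80: 13.5 points.

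At 80% DFS, the loss implied by HR 1.5 is 80 − 71.6 = 8.4 points, which lies inside the half-width. The ypT2 patients are a subset, so precision there is worse.

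The figures in steps 3 to 6 assume an intact randomised comparison. They do not allow for the regrouping and exclusion of LE patients described under the experimental arm.

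**The case against.** Several points on the other side are right.

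- Oncologic outcomes are labelled secondary in both endpoint lists. The only stated hypothesis concerns complications, and the Abstract speaks of comparing outcomes. Sizing a trial on its primary endpoint and having low power for secondary survival endpoints is ordinary, and is no fault in itself.
- The log-rank test is not the whole oncologic analysis. Kaplan-Meier estimates are planned and the endpoints are percentages at 3 years.
- Confidence intervals for secondary endpoints may be in a full protocol or analysis plan that is not shown, so their absence from the article is not held against it.
- The DFS values and hazard ratios above come from outside the document.

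Three stronger readings are tempting, and the document does not support them. One is that the investigators will declare LE oncologically safe if p > 0.05. No such rule is stated, and the Discussion itself says that evidence for LE in ypT2 is still lacking. A second is that the protocol prescribes a superiority test; it names log-rank tests only. The third is that a non-significant result is likely whatever the harm. At HR 2 and 80% DFS the test would reject slightly more often than not.

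What stands is the mismatch in the published text. The Objective and the ypT2 sentence promise a determination that a log-rank test without a margin, at this size, cannot give. An unseen analysis plan would not correct those sentences.

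**Conclusion.** The concern holds as a mismatch between the stated oncologic purpose and what the design can show. A test of difference with no margin cannot establish that LE is not worse, whatever its power.

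The size of the problem depends on an assumed DFS. For TME 3-year DFS of 90% to 60% and a true hazard ratio of 1.5, two-sided power is about 13% to 36%. A non-significant result therefore remains the likelier outcome across that range, and also under a one-sided 0.05 test (power 21% to 48%). The direction does not hinge on the exact DFS, but it does depend on the hazard ratio chosen.

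The point should be acted on, because the change is cheap and alters what the trial may claim. It is not a reason to enlarge the trial.

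**What to change.** 1. Reword the Objective so that the confirmatory claim is limited to 30-day complications and oncologic outcomes are estimated. Reword the ypT2 sentence in the Discussion in the same way.
2. Make the main oncologic result the difference in 3-year DFS, OS and recurrence (or the hazard ratio), each with a 95% confidence interval. Keep the log-rank test as supporting information.
3. Compute these in the arms as randomised, without moving completion-TME patients to the TME group and without excluding those who decline. The Data analysis section already defines an ITT set of all randomised subjects, but it assigns the endpoints to a modified ITT set. Without this step the interval could not be read as a randomised comparison.
4. State that a non-significant log-rank test will not be taken as evidence of oncologic safety or equivalence.

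The cost is wording, one interval per endpoint and a weaker headline claim. No extra patients or follow-up visits are needed.

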### Primary outcome measures

All complications within 30 days of the surgical intervention will be assessed using the Clavien-Dindo Classification Grade.

### Secondary outcomes measures

Secondary outcomes will be as follows:Oncologic outcomes: 3-year disease-free survival (% DFS), 3-year overall survival (% OS), and recurrence rate (%).Functional outcomes: quality of life, as measured using EORTC QLQ-C30 (version 3) and rectal function, as measured using manometry, low anterior resection syndrome (LARS) score, and the Wexner Fecal Incontinence Score.The rate of permanent stoma formation (%).Factors affecting complete remission and the accuracy of mrTRG.Oncologic outcome in patient subgroups.

### Study design

A prospective, double-arm, randomized, open-labeled, single center, clinical trial was initiated at Asan Medical Center, Seoul, Korea beginning in July 2017. (Fig. 1).

**Fig. 1 Fig1:**
[figure not shown]
Study design including primary and secondary study endpoints

### Study population

Patients who were diagnosed with pathologically confirmed rectal adenocarcinoma < 8 cm from the anal verge with clinically T3 or N+ before pre-CRT and an mrTRG grade 1 or 2 based on post-CRT images will be eligible for the study when they meet the following inclusion criteria:Male and female patients between the age of 20 and 80;Good performance status (ECOG performance status < 2);Capable of providing informed consent.

### Exclusion criteria

Rectal cancer > 8 cm from the anal verge;Microperforated lesion before pre-CRT;Concurrent metastasis at a diagnosis;Synchronous colorectal cancer;Previous history of radiotherapy;Other synchronous or metachronous malignancies diagnosed within 5 years of the diagnosis of rectal cancer;Enrollment in other clinical trials except for those of adjuvant therapies;Pregnant or breastfeeding women.

### Pre-registration procedures

#### Preoperative chemoradiotherapy

Pre-CRT was delivered at 50.4 Gy to the primary tumor and the pelvis in 25 fractions. Concurrent chemotherapy during radiotherapy consisted of 5-fluorouracil (5-FU; 375 mg/m^2^/day) and leucovorin (LV; 20 mg/m^2^/day) or capecitabine (825 mg/m^2^). 5-FU and LV were given on three consecutive days for two courses during the first and fifth weeks of radiotherapy, while capecitabine was given twice daily during the entire radiotherapy period without a weekend break.

#### Preoperative restaging

For assessing the pre-CRT response, digital rectal examination, sigmoidoscopy, abdomino-pelvic computed tomography (CT), chest CT, trans-rectal ultrasonography and MRI were performed within 2 weeks before surgery. Two board-certified abdominal radiologists independently assessed the response to CRT on post-CRT MRI using mrTRG (1–5) according to published definitions: 1, complete radiologic response; 2, dense fibrosis with no obvious residual tumor; 3, > 50% fibrosis or mucin with visible residual tumor; 4, small areas of fibrosis or mucin but mostly tumor, or tumor growth; 5, same appearance as baseline. The enrollment of a study cohort requires a multidisciplinary team including a colorectal surgeon, medical oncologist, radiation oncologist, and radiologist.

### Treatment strategies

#### Standard care of the control arm

TME is the standard treatment and is undertaken 6–8 weeks after the completion of pre-CRT. All operations were performed by experienced colorectal surgeons (> 100 rectal cancer cases per year). Temporary diverting ileostomy is occasionally performed in cases of a very low anastomotic level with considerable tension, air leak, or severe comorbidities. We do not perform lateral lymph node dissection routinely.

#### Investigational treatment of the experimental arm

LE will be performed via conventional transanal excision or transanal minimal invasive surgery. During LE, remnant scar tissue will be excised with at least a 1 cm resection margin. Patients who have poorly differentiated or mucinous ypT2 tumors with lympho-vascular invasion, perineural invasion, tumor budding, and close resection margins (< 1 mm) will be recommend for TME within 3 months. If the patient undergoes TME, he or she will be evaluated as part of the TME group. If the patient does not choose to undergo TME, he or she will be excluded from the study and followed-up for additional subgroup analysis.

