#### Primary outcome

The primary endpoint of the current study is the rate of postoperative complications. Postoperative events occurring up to 30 days after surgery will be evaluated by the Clavien-Dindo Classification, any events grade 2 or higher will be considered postoperative complications.

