#### Randomization and data management

After checking the response of pre-CRT, the participants with mrTRG 1 or 2 tumor will be assigned using random-number table with sealed envelopes by an external research worker who control the data. According to mrTRG 1 or 2, the allocation sequence will be stratified. The external research worker will collect the data and a statistician who provided the sample size calculation and data analysis plan will be analyze the data. The data entry, coding, security and storage with backup will be processed by the external research worker and simultaneously the statistician will check the accuracy and the value of the data. After finishing the collection of data, the external research worker, the statistician will access the dataset and investigators will access after analyses of the dataset.

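### LE-arm patients with adverse pathology are analysed as TME or excluded after randomisation, a one-sided rule that breaks the randomised comparison and conflicts with the analysis set for the endpoints

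*Protocol article*

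**What the plan says.** Allocation takes place after the restaging MRI and before any surgical specimen exists: "After checking the response of pre-CRT, the participants with mrTRG 1 or 2 tumor will be assigned using random-number table with sealed envelopes" (Protocol article, Randomization and data management).

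Under Investigational treatment of the experimental arm, LE patients with listed adverse features are advised to have TME within 3 months. For those who have it: "If the patient undergoes TME, he or she will be evaluated as part of the TME group". For those who do not: "If the patient does not choose to undergo TME, he or she will be excluded from the study and followed-up for additional subgroup analysis". Nothing comparable is written for the TME arm.

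The Data analysis section defines three sets. "The intent-to-treat (ITT) analysis set will include all subjects who are randomized into a surgery group", but that set is assigned only to baseline characteristics. The primary and secondary endpoints use a modified ITT set, defined by having received pre-CRT. The per-protocol set serves subgroup analysis.

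The primary endpoint is grade 2 or higher complications: "Postoperative events occurring up to 30 days after surgery will be evaluated by the Clavien-Dindo Classification" (Primary outcome). The section does not say which operation starts the window when a patient has two.

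The only figure on how often completion TME might arise is in the Background: "the projected completion TME rate of mrTRG1 was 25.6" percent.

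**The concern.** Randomisation makes the arms comparable only while patients stay where they were allocated. Here a result obtained after LE decides whether an LE patient remains in the LE group, moves to the comparator or leaves the study. A TME patient with the same pathology stays in the TME group. The LE group loses part of its worse-prognosis fraction. The TME group keeps its own and may receive LE's as well.

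At stake are the oncologic endpoints (disease-free survival, overall survival, recurrence) and permanent stoma, since stomas made at completion TME would be counted in the TME group. The Discussion also says that "our study determines the effect of LE in ypT2 tumors on oncologic outcomes", an aim that is narrowed when higher-risk ypT2 patients leave the LE group.

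**Working it through.** **1. Do the sections agree?** Pre-CRT precedes randomisation, so every randomised patient meets the modified ITT definition. That set keeps the decliners whom the treatment section excludes: a direct conflict. It does not say that patients are analysed as allocated, so it does not cancel the move to the TME group. The ITT set would, but no endpoint is assigned to it.

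**2. How many patients?** The documents plan 67 per group. Let *f* be the share of LE patients affected. At *f* = 0.256, 67 × 0.256 = 17.2 patients. If all have TME, the groups become about 50 v 84. If all decline, they become about 50 v 67. The 5% dropout allowance does not cover that. The value of *f* is an assumption: 25.6% refers to mrTRG1 only, whereas mrTRG 2 is also enrolled, so 10% and 35% are shown too. The trigger is not settled either: the Safety section adds ypT3 and ypT4 to the ypT2 criteria in the treatment section.

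**3. Oncologic endpoints with no true treatment effect.** Let *D* be the gap in 3-year disease-free survival between favourable and adverse pathology. The documents give no value, so 90% v 65–75% is assumed (*D* = 15–25 points).

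- All decline and are excluded: spurious LE advantage = *f* × *D*.
- All have TME and are moved: 2*fD*/(1 + *f*).

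At *f* = 0.256 and 90% v 65%, both arms are truly 0.744 × 90 + 0.256 × 65 = 83.6%. Under the rule the LE group shows 90%. The TME group shows 83.6% if all are excluded, or (67 × 83.6 + 17.2 × 65)/84.2 = 79.8% if all are moved. At 90% v 75% the true value is 86.2%, and the TME group shows 86.2% or 83.9%.

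| Share affected | All excluded | All moved |
|---|---|---|
| 10% | 1.5–2.5 | 2.7–4.5 |
| 25.6% | 3.8–6.4 | 6.1–10.2 |
| 35% | 5.3–8.8 | 7.8–13.0 |

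(Points in favour of LE.)

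**4. Permanent stoma.** If completion TME carried the roughly 30% permanent-stoma rate that the Discussion reports for TME after pre-CRT (an assumption), 0.256 × 30% = 7.7 points of stoma arising in patients allocated to LE would be absent from the LE group.

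**5. Thirty-day complications, reassignment alone.** Take the protocol's 15% v 15%, assume complications are unrelated to pathology, and let *q* be the complication rate of completion TME (not given in the documents). If only the completion-TME event counts for a moved patient, LE minus TME = *f*(0.15 − *q*)/(1 + *f*). If the earlier LE event is carried along as well, replace *q* by 1 − 0.85(1 − *q*). At *f* = 0.256:

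| *q* | Completion-TME event only | Both events carried |
|---|---|---|
| 10% | +1.0 | −1.7 |
| 15% | 0 | −2.6 |
| 30% | −3.1 | −5.2 |

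(Percentage points; negative favours LE. The margin is 15 points.)

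Exact enumeration with a one-sided 95% Wald limit, LE truly at 30% v 15%, gives a false non-inferiority rate of 0.052 as randomised. Under the rule (completion-TME event only) it is 0.046, 0.060 and 0.118 for *q* = 10%, 15% and 30%.

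**6. If both operations count in the LE arm as allocated.** LE risk = 1 − 0.85(1 − 0.256*q*) = 18.3% (*q* = 15%) or 21.5% (*q* = 30%). As a baseline, the planned 67 is not reproduced exactly: the normal approximation at 15% v 15% gives 71 per group and 78.4% power at 67, which is a separate matter. At 67 per arm, power falls to about 57% and 36% respectively.

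**The case against.** The strongest reply is that the primary endpoint may hardly be affected. That largely stands for reassignment alone. If completion TME is as risky as primary TME and the earlier LE event is dropped, the shift is nil; if it is safer, the rule works slightly against LE. A reader might infer that every comparison, the primary one included, is biased towards LE. The documents do not support that, because they give no complication rate for completion TME.

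A reader might also set the plan's rule (0 to 3.1 points better for LE) against an as-allocated analysis that charges both operations to LE (3.3 to 6.5 points worse) and report a swing of 3.3 to 9.6 points. Most of that comes from changing the endpoint: reassignment contributes only the 0 to 3.1.

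Other limits stand. The 25.6% is a projection for mrTRG1, so 17 of 67 is a scenario and not the protocol's own expectation. LE does not keep only good responders, since ypT2 without the listed features stays. The ypT2 aim is narrowed, not defeated, and decliners are still followed for a subgroup analysis.

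Finally, one might say that the ITT definition already protects the comparison. It does not, because it is assigned only to baseline characteristics.

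**Conclusion.** The concern holds. The reassignment and exclusion are explicit, apply to one arm, depend on a prognostic result after randomisation, and are not overridden elsewhere. The exclusion contradicts the modified ITT set.

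For disease-free survival, overall survival and recurrence the direction is towards LE whenever adverse pathology carries a worse prognosis. The protocol leans that way itself: it describes pCR and ypT1N0M0 as more favourable, and nodal infiltration and local recurrence in ypT2 as worrisome. The sizes rest on the assumed share affected and the assumed survival gap. For 30-day complications the direction is conditional on the completion-TME rate and on which events count; only the ambiguity is certain.

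**What to change.** Replace the two sentences on evaluation and exclusion in the experimental-arm section, and the modified ITT sentences in Data analysis, with:

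> All randomised patients are analysed for the primary and secondary endpoints in the arm to which they were allocated, whatever the pathology and whether completion TME is done or declined; no patient is excluded for declining.

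Keep as-treated and per-protocol comparisons as labelled sensitivity analyses, and report the completion TME rate. State which operation starts the 30-day window, and report complications of completion TME under the LE arm. The triggers for completion TME in the experimental-arm and Safety sections differ and must be reconciled.

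Cost: analysing as allocated is a change of wording and needs no new data, because a decliner is already to be "he or she will be excluded from the study and followed-up for additional subgroup analysis". LE results may look less favourable. Counting completion-TME events in the primary endpoint is a separate and dearer choice: it gives some LE patients two 30-day windows, and the assumed LE rate, power and sample size would have to be restated.
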